## Abstract

**Background:**

Respiratory tract infections in children result in more primary care consultations than any other acute condition, and are the most common reason for prescribing antibiotics (which are largely unnecessary). About a fifth of children consult again for the same illness episode. Providing parents with written information on respiratory tract infections may result in a reduction in re-consultation rates and antibiotic prescribing for these illnesses. Asking clinicians to provide and discuss the information during the consultation may enhance effectiveness. This paper outlines the protocol for a study designed to evaluate the use of a booklet on respiratory tract infections in children within primary care consultations.

**Methods/Design:**

This will be a cluster randomised controlled trial. General practices will be randomised to provide parents consulting because their child has an acute respiratory tract infection with either an interactive booklet, or usual care. The booklet provides information on the expected duration of their child's illness, the likely benefits of various treatment options, signs and symptoms that should prompt re-consultation, and symptomatic treatment advice. It has been designed for use within the consultation and aims to enhance communication through the use of specific prompts. Clinicians randomised to using the interactive booklet will receive online training in its use. Outcomes will be assessed via a telephone interview with the parent two weeks after first consulting. The primary outcome will be the proportion of children who re-consult for the same illness episode. Secondary outcomes include: antibiotic use, parental satisfaction and enablement, and illness costs. Consultation rates for respiratory tract infections for the subsequent year will be assessed by a review of practice notes.

**Discussion:**

Previous studies in adults and children have shown that educational interventions can result in reductions in re-consultation rates and use of antibiotics for respiratory tract infections. This will be the first study to determine whether providing parents with a booklet on respiratory tract infections in children, and discussing it with them during the consultation, reduces re-consultations and antibiotic use for the same illness without reducing satisfaction with care.

**Trial registration:**

Current Controlled Trials ISRCTN46104365

## Background

Acute respiratory tract infections (RTIs) are the most common illnesses experienced by individuals of all ages worldwide [1]. Children, who experience more illness episodes than any other age group, will on average have between five and six respiratory infections per year [1]. In the United Kingdom, 97% of pre-school age children will consult with a doctor at some point, mostly for symptoms related to respiratory tract infections [2]. These illnesses are the most common reason for patients to consult in primary care, and children consult more than any other age group [3]. In addition, around one in five children consulting because of a RTI will re-consult for the same illness episode [4], a proportion that has changed little over the past thirty years [5]. Parents frequently describe anxiety and disempowerment when coping with respiratory tract infections in their children [6,7]. These problems may be addressed by the provision of clear, reliable information [7,8].

Furthermore, most respiratory tract infections benefit very little from treatment with antibiotics [9-13], yet their use continues to be widespread [14,15] with children receiving more antibiotics than any other age group [16]. Approximately 25% of consultations with children with a RTI result in an antibiotic prescription [16], and approximately half of all children aged 0 – 4 will receive an antibiotic prescription in any one year period [17]. Unnecessary antibiotic prescribing results in wasted healthcare resources, leads to a cycle that encourages further consulting in the future for similar illnesses [18] and contributes to the problem of antibiotic resistance [19].

Parental factors influencing the decision to consult include concerns, knowledge, beliefs, and expectations. Parents often fear serious illness, and worry that they will not be able to recognise symptoms of serious illness [6]. Despite their concerns, a number of parents worry about 'bothering' their general practitioner with these illnesses [20,21]. They also lack knowledge about the likely risks and benefits from antibiotic treatment, and the normal duration of illness [22]. Patients may hold beliefs about the causes of respiratory tract infections [22-24], the meaning of symptoms [25,26], and the effectiveness of medications [22,23,25,27], that are at odds with biomedicine.

Providing parents with written information about respiratory tract infections in children may help alleviate anxiety and improve parental feelings of satisfaction and enablement. In adults, the use of leaflets describing the expected duration of symptoms and giving advice about self-help for lower respiratory tract infections, has resulted in reductions in re-consultations [28] and antibiotic prescribing [29].

Expectations that patients (and parents) bring to consultations can have an impact on outcomes. There is an increased likelihood that antibiotics will be prescribed when parents consult with expectations for an antibiotic prescription [30]. However, clinicians seldom explicitly enquire about expectations [31], and often over-estimate the expectation for antibiotics [21]. A clinician's perception of an expectation for antibiotics is associated with an even greater likelihood of prescribing than actual patient expectations [30,32]. Parents value a thorough examination, explanation, reassurance and advice or guidance more than a prescription for antibiotics [21,33].

Other studies have evaluated the use of printed patient information on respiratory tract infections. Sending booklets on a range of minor illnesses (including respiratory tract infections) to patients' homes has been shown to have little impact on consultation rates in a number of studies [34-38]. However, an editorial accompanying the two most recent of these studies suggested that the use of written material to support the management of minor illnesses was more likely to be of value if it was used within the consultation and was context-specific [39].

A study conducted in the 1980's in one health centre in the United States showed a reduction in consultation rates for patients provided with a pack containing a pamphlet, sticker and thermometer [40]. However, this study was limited by non-random allocation, and post-allocation exclusion of subjects with chronic illnesses. In another US study, parents were randomised to receive educational materials on either the use of antibiotics or injury prevention [41]. There were no differences in consultation rates or antibiotic prescribing between these two groups, which may reflect the need to provide parents with positive information about managing an illnesses rather than a negative message about a treatment option (antibiotics). A more recent non-randomised US study examined the role of patient educational materials and providing clinicians with prescribing profiles and practice guidelines [42]. This led to reductions in antibiotic prescribing for bronchitis in adults, but not for paediatric pharyngitis.

Printed educational materials have frequently been used as part of larger multi-faceted interventions [43-48]. A number of these interventions have been associated with either a reduction in prescribing or improvements in parental knowledge and awareness about antibiotics. However, it is not possible to determine the role of the educational materials within these complex interventions, and in none of these studies were the materials designed for use specifically within the consultation.

We set out to address high levels of consulting and antibiotic prescribing, and parental disempowerment and dissatisfaction, by developing a booklet on respiratory tract infections in children, designed to be used within primary care consultations and then provided to parents as a take-home resource. The booklet and clinician training have theoretical roots in Social Cognitive Theory [49,50] and the Theory of Planned Behaviour [51,52]. The key aspects of these theories incorporated in the intervention are outcome and efficacy expectations. Behaviour change is more likely if the individual believes in the importance or value of change (outcome expectations) and feels that they have the confidence or skills to change (efficacy expectations). To enhance the likelihood that the intervention will result in reductions in health service utilisation and antibiotic prescribing it has been aimed at both clinicians and parents. Clinicians are provided with information about the implications of high levels of consulting and antibiotic use, in order to increase outcome expectations. They are also provided with specific tools to facilitate change (efficacy expectations). These tools include communications strategies provided within the training programme, and the study booklet, which acts as an aide memoir and a prompt to enhance communication within the consultation. Similarly, we aim to influence the behaviour of parents by providing them with information about the importance of change (benefits of self-management and implications of overuse of antibiotics), and by attempting to enhance their confidence and skills. We aim to achieve the latter through use of the study booklet which encourages them to have their concerns addressed within the consultation, and provides them with clear, relevant information about their child's illness.

### Main research questions

Our main aim is to determine whether the pragmatic use of this intervention can result in a reduction in the proportion of children who re-consult during the same illness episode. We will also examine the impact that use of this intervention has on: antibiotic prescribing and use, parental satisfaction, parental enablement, intention to consult with a similar illness in the future, illness costs, and consultation rates for RTIs over the following year. In this paper we describe the study protocol.

## Methods

This will be a cluster randomised controlled trial with randomisation at the level of the general practice. Recruited general medical practices will be randomised to one of two arms; use of an interactive booklet or usual care (see Figure 1).

**Figure 1 F1:**
[figure not shown]
Study flow chart.

### The intervention

The study booklet was developed through a multi-stage process, which is outlined below and will be reported in full elsewhere.

The aims and broad content areas were decided through a number of 'brainstorming' sessions held by a multidisciplinary development group. Systematic searches were undertaken to identify existing patient information leaflets and literature on development of patient educational materials, management of respiratory tract infections in children, healthcare communication and shared decision-making. These materials were reviewed and synthesised, and a draft booklet (2 sides of A4 paper) was developed. This was presented to a number of parent focus groups, individual parents through an interview process, and two general practitioner focus groups. In addition, six practising academic GPs, two practising paediatricians, and a 'basic skills professional', who focused on improving readability, reviewed the emerging booklet. This process led to important changes to content and design. The design was also enhanced through input from a professional graphic designer. The end result was an eight-page A5 booklet, the content of which is summarised in Table 1.

**Table 1 T1:** Summary of study booklet content

**Section name**	**Contents**
**Who is this booklet for?**	General introduction and advice on who the leaflet does not apply to (under 6 months, children with chronic illnesses)
**Prompts**	Prompts to remind the practitioner (and the parent) to discuss the parent's main concerns and their expectations.
**Fever**	Facts about fever and advice on managing it.
**Temperature fits (Febrile Seizures)**	General information and advice on management.
**Cough/Chesty Cough**	General information, graphical representation of normal duration, advice about management, and information about the effectiveness of antibiotics.
**Common Cold**	Information about frequency and graphical representation of normal duration. Advice on the effectiveness of antibiotics.
**Green phlegm/Snot**	Advice about the interpretation of discoloured nasal discharge.
**Sore Throat**	General advice, graphical representation of the normal duration, information about the effectiveness of antibiotics.
**Earache**	General advice, graphical representation of the normal duration, information about the effectiveness of antibiotics.
**Croup**	Information about symptoms and management (including signs of respiratory distress) and the effectiveness of antibiotics.
**Not Eating/Drinking**	Advice on these symptoms including signs of dehydration.
**What can I do?**	General section on management advice.
**Why not take antibiotics?**	Information about the potential disadvantages to use of antibiotics.
**When should I seek further help?**	Comprehensive section providing a description of symptoms and signs suggestive of serious illness, including pictures of a meningitis/septicaemia rash (and the 'tumbler test'). Also advice on other situations that should prompt re-consultation.
**Contact details**	Space for clinicians to write 'in-hours' and 'out-of-hours' contact numbers. Contact details for NHS direct (national health information service).

The aims of the interactive booklet are to act as an evidence-based information resource for parents, an aide memoir for clinicians, a tool to help set realistic expectations, and a prompt to enhance communication within the consultation. The booklet is described as 'interactive' because it has been designed for use within consultations to facilitate interaction between the clinician and the parent. It aims to achieve this by providing specific prompts which encourage discussion of the parent's main worries, and their expectations for the consultation. In addition, the booklet includes boxes and spaces, which allow for personalisation.

### Clinician training

All participating clinicians will be provided with training in study processes. This includes the background and aims of the study, how to recruit patients, inclusion and exclusion criteria, obtaining informed consent (including determining when a child should be asked to provide consent), and how to complete the patient encounter sheet (including the importance of accurate data collection). This training will be provided through a dedicated website, accessed by means of a username and password provided to all participating clinicians [53].

In addition to the training in study processes, clinicians in practices randomised to the intervention arm will complete a training module on use of the study intervention (booklet) within their consultations. Unique log-in details provided to these practitioners will automatically ensure that they are provided access to the additional training module. This training describes the contents of the booklet, encourages its use within the consultation, and encourages clinicians to use the booklet to facilitate the use of certain communication skills; namely exploring the parents' main concerns, asking about their expectations, and discussing prognosis, treatment options, and what should prompt re-consultation. The training incorporates videos that demonstrate use of the booklet in a consultation, as well as audio feeds, pictures, and links to study materials. This part of the training will take approximately 40 minutes to complete.

Clinician training will be monitored through the study website. This will allow the study team to identify whether a clinician has logged on to the site, how much time they spent on it, and which pages they have viewed. This will allow for a reasonable assessment of whether or not participating clinicians are completing the required training. Clinicians will be asked to complete all their required training before starting to recruit patients.

### Sample size estimation

The primary outcome is re-consultation for the same illness episode. In order to show a reduction in the proportion of children re-consulting from 20% to 10%, with 80% power, and a 5% significance level, we would require 438 participants for an individually randomised trial. From a previous study of upper respiratory tract infections in children [4], we calculated an intra-cluster coefficient of 0.04 for re-consultation rates. Using 60 clusters (practices) we would need 524 participants to have the same power as an individually randomised trial. To allow for loss to follow-up and missing data we have decided on a target recruitment of 600 participants, 10 from each practice.

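### The cluster-adjusted size of 524 does not follow from 438, an ICC of 0.04 and 60 practices, which give 594; the two figures appear to rest on different bases

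*Protocol article*

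**What the plan says.** All the figures stand in one paragraph of the protocol article, under Sample size estimation. The target is a fall in re-consultation from 20% to 10%, "with 80% power, and a 5% significance level", for which "we would require 438 participants for an individually randomised trial". From an earlier study of upper respiratory infections in children, "we calculated an intra-cluster coefficient of 0.04 for re-consultation rates". The clustering step follows: "Using 60 clusters (practices) we would need 524 participants to have the same power as an individually randomised trial". The recruitment target is built on that result: "To allow for loss to follow-up and missing data we have decided on a target recruitment of 600 participants, 10 from each practice".

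The paragraph names no formula, sidedness, allocation ratio or percentage loss. The Analysis section plans a two-level logistic model for the primary outcome.

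**The concern.** The paragraph runs as a chain: individual size, inflation for clustering, addition for loss. The second link does not follow from the first. The rise from 438 to 524 is a factor of 1.196, but 60 practices of eight to ten children with an ICC of 0.04 give a design effect of about 1.3 to 1.36.

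What is at stake is how the 600 should be read. If 524 evaluable children are enough, 600 leaves room for 76 losses. If 438 is the true individual requirement, almost the whole of 600 is needed for analysis, and the allowance for loss and missing data nearly disappears. A reader cannot tell from the paragraph which of these the investigators intended.

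**Working it through.** **Inputs** (Sample size estimation): 20% v 10%; power 80%; significance 5%; individual total 438; ICC 0.04; 60 practices; clustered total 524; recruitment 600. Assumed: two-sided test, 1:1 allocation, equal numbers per practice.

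**1. Reproduce 438.** Pooled-variance formula per arm, with mean proportion 0.15:

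n = [1.960 × √(2 × 0.15 × 0.85) + 0.842 × √(0.20 × 0.80 + 0.10 × 0.90)]² / 0.10² = 198.96, so 199 per arm, 398 in total.

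With continuity correction: n/4 × [1 + √(1 + 4/(n × 0.10))]² = 218.5, so 219 per arm, **438 in total**. The printed figure is therefore exactly the two-sided, continuity-corrected size. The other variants do not match: unpooled 394; one-sided 314, or 354 with correction.

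**2. Inflate for clustering.** With total N spread over 60 practices, N = n × [1 + (N/60 − 1) × 0.04], which solves to N = 0.96n / (1 − 0.04n/60).

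| Individual total n | Clustered total N | Per practice |
|---|---|---|
| 438 | 420.48 / 0.708 = 593.9 (594) | 9.90 |
| 400 | 384 / 0.7333 = 523.6 (524) | 8.73 |
| 398 | 382.08 / 0.7347 = 520.1 | 8.67 |

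**3. Try other conventions from 438.** One-step design effects also miss 524:
- cluster size 438/60 = 7.3 gives 548
- cluster size 524/60 = 8.73 gives 573
- cluster size 10 gives 438 × 1.36 = 596

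To reach 524 from 438 at 8.73 per practice, the ICC would have to be (524/438 − 1)/(8.73 − 1) = 0.025. At an ICC of 0.04 it would take about 89 practices. Rounding of the ICC does not explain the gap, since 0.035 still gives 568.

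**4. What 524 delivers.** Design effect 1 + (8.73 − 1) × 0.04 = 1.309; effective size 524/1.309 = 400.

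| Effective size | Power, no continuity correction | Power, continuity-corrected |
|---|---|---|
| 438 | 83.7% | 80.1% |
| 400 (524 in 60 practices) | 80.2% | 76.1% |

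The shortfall against the 438-participant trial is about 3.4 points (83.65 − 80.22) or 4.0 points (80.10 − 76.06).

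**5. Loss allowance at 600.** On the 524 requirement: 76/600 = 12.7%. On the 594 requirement: 6/600 = 1%. At 10% loss (540 evaluable, 9 per practice, design effect 1.32, effective size 409), power is 81.1% without correction and 77.1% with it.

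**The case against.** The strongest reply is that the operative numbers are sound. The planned logistic model uses no continuity correction. On that basis 524 evaluable children give 80.2% power and 600 recruited allows 12.7% loss, so power, evaluable number and allowance all hold together. The only figure out of line is 438, an intermediate comparator that sets no target. The phrase about having the same power can also be read as the nominal 80%, which 524 then delivers.

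Most of this stands. A reader might infer from the gap between 524 and 594 that the trial is underpowered, or that the stated power, evaluable number and loss allowance are incompatible. The document does not support either inference. Power of 76% at 524, and an allowance of 1%, arise only if the continuity-corrected 438 is kept as the basis.

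The reply does not make the paragraph consistent. The only individually randomised trial it describes has 438 participants, and 524 does not match that trial's power with or without the correction. If the nominal-80% reading is meant, 438 is the wrong comparator. One printed figure has to change either way. Nor can this be put down to detail left to a fuller document, because the figures that disagree are all printed together.

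**Conclusion.** The sample-size paragraph is wrong as written. From 438, an ICC of 0.04 and 60 practices the clustered size is 594, which is 70 children (13% of 524) more than stated. The 524 corresponds to an effective size of about 400 and has about 3.4 to 4 points less power than the 438-participant trial.

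The likely explanation is a change of basis between the two steps: 438 matches the continuity-corrected size exactly, and 524 matches an uncorrected 200 per arm. This is inferred from the match, since the protocol names no formula.

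It is an error in a figure on which the recruitment target rests, but not a demonstrated loss of power. Without continuity correction, about 80% power is kept at 524 evaluable. These results assume two-sided testing, 1:1 allocation and equal cluster sizes; unequal recruitment between practices would raise the requirement on either basis.

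**What to change.** Use one basis throughout the paragraph, name it, and restate the figures.

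- **Preferred:** replace 438 with 400 (200 per arm, no continuity correction, in keeping with the planned logistic model). Keep 524 evaluable and 600 recruited, and state the loss allowance of about 12.7%. Equivalently, state 398 leading to 520, with an allowance of 80/600 = 13.3%. Pairing 398 with 524 would leave a small mismatch.
- **Otherwise:** keep 438 as a continuity-corrected size and change 524 to 594. State that 600 then allows only about 1% loss and that power at 524 evaluable would be about 76% on that basis. Keeping a 12.7% allowance as well would mean recruiting about 594/(524/600) = 680, or 80 more children.

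In either case, state the sidedness and allocation ratio. The preferred option costs one reworded paragraph and no extra participants.
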